### Data Analysis Plan

#### Primary Noninferiority Analysis

We hypothesize that the intervention arms incorporating the digital delivery intervention, with access to a GC upon request, can yield equal or improved short-term and longitudinal cognitive, affective, and behavioral outcomes and lower health care provider time. Our primary outcomes are change between T0 and T2 in knowledge and anxiety. We will test whether the digital intervention is noninferior to standard-of-care counseling with a GC. In noninferiority tests, the null and alternative hypotheses are the reverse of the usual; in this case, the null hypothesis is that the web intervention is worse than the standard of care. We will conclude that the web intervention is noninferior using a modified noninferiority ANOVA of the T2 minus T0 change scores. More details on the power and type I error are provided in the following section. We will use an intention-to-treat approach comparing randomization arms, but we will also confirm results in secondary per-protocol analyses; many recommend that both intention-to-treat and per-protocol analyses be consistent to declare noninferiority [71]. In secondary analyses, we will test pairwise differences among the 4 groups. For longitudinal analyses across the 3 survey times (T0-T3), we will examine time trajectories using regressions estimated through generalized estimating equations to account for within-subject correlation over time. We will include main and interaction terms of arm with time panel indicators.

Our noninferiority test will be based on an ANOVA *F* statistic test jointly comparing the 4 randomization arms, in which we declare noninferiority if the joint *P* value is of >.15 and all 3 experimental web arms have an observed standardized effect of −0.25 SD units or better (with the direction standardized such that higher values imply more beneficial change) when compared to the control standard of care–only arm. If the ANOVA *F* test *P* value is ≤.15, then we will declare noninferiority if the 3 standardized one-sided 85% confidence bounds for the 3 intervention arms relative to the controls are >−0.35 SDs. We define standardization as rescaling variables to have an SD of 1 relative to the pooled baseline SD (see more details in the following section).

#### Sample Size Justification for Aim 1

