We originally anticipated 140 participants per arm (560 in total). We chose our 2 primary variables as they demonstrated possible differences between groups in preliminary data from a prior study in which genetic test results were returned to patients; in this study, we expect that harmful changes will not occur. We will use a noninferiority test and, to be conservative, will require noninferiority in both the intention-to-treat and per-protocol analyses, as recommended [71].

With 140 people per arm, we have <1% noninferiority type I error and >82% noninferiority power if we simply use the first criteria that the *P* value must be >.15 and all 3 intervention arm coefficients must be >−0.25 (ie, in the direction away from being harmful when compared to the standard-of-care group). If we further apply the decision rule that the 85% one-sided CIs are bounded away from −0.35 if *P*≤.15, the power increases to 94%, and the type I error rate remains at <1%.

In calculating the type I error rate, we assumed that the 4–change score standardized means (standardized to have an SD of 1) for the null hypothesis were 0 (arm A=control group), 0.3 (single web intervention arms), and −0.6 (double web intervention arm), with negative values indicating a harmful effect. Our alternative hypothesis was a null effect (4–change score means of 0). These were conservative estimates of changes based on standardized RESPECT web intervention findings of a change score movement of 0.3 in anxiety and a change score movement of 0.4 in knowledge. Hence, we have excellent noninferiority power. Calculations were made using PASS (version 11; NCSS Statistical Software) in conjunction with R simulations (R Foundation for Statistical Computing). In secondary analyses, we will examine pairwise comparisons among the 4 arms using 2-tailed *t* tests.

In Multimedia Appendix 1, we provide the probability of declaring noninferiority under a range of assumptions about the intervention effects relative to the standard-of-care control arm. We see that our probability of declaring noninferiority is appropriate under several assumptions about population-level mean differences among arms.

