**Original assumptions (unconditional on observed data)**						
	No effect (power)	0	0	0	0	79
	Arm B and arm C beneficial	0	0.2	0.2	0	86
	Web intervention slightly beneficial	0	0.1	0.1	0.1	92
	Heterogeneous effects	0	−0.1	0.1	0	71
	Web intervention slightly harmful	0	−0.1	−0.1	−0.1	59
	Web intervention harmful—small effect	0	−0.2	−0.2	−0.2	36
	Web intervention harmful—relatively small effect	0	−0.25	−0.25	−0.25	25
	Web intervention harmful—modest effect	0	−0.3	−0.3	−0.3	16
	Only Arm B harmful	0	−0.35	0	0	23
	Web intervention harmful—moderate effect	0	−0.35	−0.35	−0.35	9
	Arm D very harmful (type I error)	0	−0.3	−0.3	−0.6	2

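### The stated type I error (<1% at 140 per arm, 2% at 60) holds only at one configuration well beyond the −0.25 SD margin; at the margin the rule can pass an inferior arm in about 43–44% of trials

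*Protocol article*

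**What the plan says.** The Primary Noninferiority Analysis section gives the null as "the null hypothesis is that the web intervention is worse than the standard of care" and sets a two-limb rule. In the first limb, "we declare noninferiority if the joint *P* value is of >.15 and all 3 experimental web arms have an observed standardized effect of −0.25" SD or better against control. In the second limb, used when the joint P value is at most .15, the authors will "declare noninferiority if the 3 standardized one-sided 85% confidence bounds for the 3 intervention arms relative to the controls are >−0.35 SDs". The end of the sample size section names −0.25 as the noninferiority margin and describes −0.35 as still modest.

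For 140 per arm, the sample size section states "we have <1% noninferiority type I error and >82% noninferiority power if we simply use the first criteria". The next sentence gives 94% power and again <1% error for both limbs together. The null used is described as 0 for control, "0.3 (single web intervention arms") and −0.6 for the double-web arm, with negative meaning harmful. After a sentence on the alternative hypothesis, the text adds "These were conservative estimates of changes based on standardized RESPECT web intervention findings", citing movements of 0.3 in anxiety and 0.4 in knowledge.

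For 60 per arm, the unconditional block of Table 5 labels one row "Arm D very harmful (type I error"), with means 0, −0.3, −0.3, −0.6 and probability 2%. The other harmful rows carry no such label. They include all web arms at −0.25 (25%), at −0.3 (16%) and at −0.35 (9%), and "Only Arm B harmful" at −0.35 (23%).

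**The concern.** A noninferiority rule that requires all three web arms to pass has a composite null: at least one arm is at or beyond the margin. Its type I error is the largest probability of a noninferiority claim anywhere in that null. This is normally reached at the boundary, with one arm on the margin and the rest near no effect. A figure taken deep inside the null describes one scenario and says little about the rule's level.

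The direction of the choice matters too. For power, assuming a less favourable truth is cautious. For type I error it is the reverse: the more harmful the assumed null, the smaller the error looks. A null with an arm at −0.6 cannot therefore be called conservative for this purpose.

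A positive result would be used to support replacing counselor visits with a digital tool, and readers will weigh it against the error rate printed in the plan.

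**Working it through.** **Inputs, all from the article.** 140 per arm (original) or 60 per arm (revised); change-score SD 1; margin −0.25; second limit −0.35; ANOVA threshold .15; one-sided 85% bounds; all three web arms must pass.

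**Method.** Monte Carlo with 400,000 trials per configuration: four normal arms, a one-way ANOVA F test, then the two limbs with pooled-variance t bounds. The worst case was sought over a grid of the other two arms' means from −0.2 to +0.2, with 100,000 trials per point.

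**Step 1: reproduce the plan.**

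| Quantity | Stated | Simulated |
|---|---|---|
| 140/arm, power, first limb | >82% | 84% |
| 140/arm, power, full rule | 94% | 94.4% |
| 140/arm, error at (0, −0.3, −0.3, −0.6) | <1% | 0.1% |
| 60/arm, power, full rule | 79% | 79.5% |
| 60/arm, error at (0, −0.3, −0.3, −0.6) | 2% | 1.9% |

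All 11 unconditional rows of Table 5 reproduce within 1 point, so the rule has been read as the authors applied it.

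**Step 2: where the stated figure sits.** −0.6 / −0.25 = 2.4, so arm D is at 2.4 times the margin; B and C, at −0.3, are also beyond it.

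**Step 3: hand check for one arm.** The SE of a difference is √(2/n): √(2/60) = 0.183 and √(2/140) = 0.120.
- First limb, true effect −0.25: the cut-off on the observed effect is the margin itself, so this condition alone is met 50% of the time at any sample size.
- Second limb: the observed effect must exceed −0.35 + 1.036 × SE, which is −0.161 (60/arm) or −0.226 (140/arm). An arm truly at −0.35 clears this 15% of the time by construction. An arm truly at −0.25 clears it with probability P(Z > 0.49) = 31% (60/arm) or P(Z > 0.20) = 42% (140/arm).
- Arm D at −0.6: it reaches −0.25 with probability P(Z > 0.35/0.183 = 1.92) = 2.8% (60/arm) or P(Z > 0.35/0.120 = 2.93) = 0.2% (140/arm). This distance is what makes the printed error small.

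**Step 4: full rule at the plan's own limits.**

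| True means of web arms | 60/arm | 140/arm |
|---|---|---|
| One at −0.25, others 0 | 43% | 44% |
| Maximum found, one at −0.25 | 43% | 44% |
| All three at −0.25 | 25% | 23% |
| One at −0.35, others 0 | 23% | 15.5% |
| Maximum found, one at −0.35 | 24% | 16.5% |
| All three at −0.35 | 9% | 5% |

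The first limb alone at 140 per arm, with the other arms at 0, gives 24% (one arm at −0.25) and 4.9% (one arm at −0.35). The <1% claimed for the first criterion is therefore also a property of the chosen configuration.

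**Step 5: sensitivity to SD.** With one arm at −0.25 and 60 per arm, the rate is 42–43% for change-score SDs from 0.8 to 1.2.

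**Step 6: the sign.** With +0.3 for B and C, as the text prints, the error at 60 per arm is 0.8%. With −0.3, as Table 5 prints, it is 1.9%, which matches the stated 2%. The calculation used −0.3.

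**The case against.** Several points on the other side are fair.

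- The printed numbers are not miscalculated. That stands: the fault lies in where the error was evaluated and what it was called.
- Table 5 openly prints 25%, 23%, 16% and 9% for harmful scenarios, and the article points to an appendix, not seen here, for the 140-per-arm equivalents. That stands as disclosure. It does not cure the label, because only the 2% row is called type I error.
- The −0.6 can be read as twice the single-web −0.3, an additive effect for the double-web arm. This is plausible, though the article does not say so, and it explains the scenario without making it the null boundary.
- The word conservative follows directly on the sentence about the alternative hypothesis, and the article later defends that alternative as conservative. The reference to harmful movements in the prior study fits the null better, but the wording is ambiguous. It needs to be limited to the alternative.
- Success is required in both the intention-to-treat and per-protocol analyses. This can only lower the rates; by how much cannot be worked out from the article. The article describes no such adjustment to its own figures, and they reproduce without one.

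A reader might also infer that the sign slip corrupted the error rates, or that the chosen configuration is the one where a false claim is hardest to make. Neither is supported. The 2% requires −0.3, and all three arms at −0.6 would give only 0.2% at 60 per arm.

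**Conclusion.** The <1% and 2% are correct for one harmful scenario and wrong as statements of the rule's type I error. At the margin the article names, the maximum is about 44% (140 per arm) and 43% (60 per arm). At the secondary −0.35 limit it is about 16.5% and 24%. Going from 60 to 140 per arm does not lower the rate at −0.25, because the first limb compares the point estimate with the margin without allowing for sampling error.

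These figures assume normal change scores with SD 1 and equal arms, and they apply to one outcome in one analysis set. They should not be read as the probability that the whole trial makes a false claim. Nor does every configuration at a limit give a high rate: all three arms at −0.35 pass in only about 9% (60 per arm) and 5% (140 per arm). Those lower values do not rescue the stated level, because the worst case governs.

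**What to change.** In the sample size section and Table 5:

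1. Replace <1%, and the type I error label on the 2% row, with the maximum error at the stated −0.25 margin: about 44% at 140 per arm and 43% at 60 per arm. Report beside it the maximum at the secondary −0.35 limit: about 16.5% and 24%. State that the rates are per outcome and per analysis set.
2. Present the row with arm D at −0.6 as one harmful scenario only.
3. Label the unconditional Table 5 rows in which at least one arm is at or beyond −0.25 as type I error rows: all arms at −0.25, −0.3 and −0.35, and arm B alone at −0.35. If the −0.6 row is kept among them, it should not stand as the headline figure.
4. Do not describe the −0.3/−0.6 null as conservative for type I error; keep that word for the no-benefit alternative.
5. Correct 0.3 to −0.3 for the single-web arms in the text, to match Table 5. No stated figure changes.

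The cost is a text and label correction with no new data. The price is a much less favourable stated error rate, which the report of results will then have to face openly.

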**Original assumptions (unconditional on observed data)**						
	No effect (power)	0	0	0	0	79
	Arm B and arm C beneficial	0	0.2	0.2	0	86
	Web intervention slightly beneficial	0	0.1	0.1	0.1	92
	Heterogeneous effects	0	−0.1	0.1	0	71
	Web intervention slightly harmful	0	−0.1	−0.1	−0.1	59
	Web intervention harmful—small effect	0	−0.2	−0.2	−0.2	36
	Web intervention harmful—relatively small effect	0	−0.25	−0.25	−0.25	25
	Web intervention harmful—modest effect	0	−0.3	−0.3	−0.3	16
	Only Arm B harmful	0	−0.35	0	0	23
	Web intervention harmful—moderate effect	0	−0.35	−0.35	−0.35	9
	Arm D very harmful (type I error)	0	−0.3	−0.3	−0.6	2
**Genetic knowledge** **—** **conditional on observed data (higher scores are better)**						
	No effect	0	0	0	0	99
	Arm B and arm C beneficial	0	0.2	0.2	0	100
	Web intervention slightly beneficial	0	0.1	0.1	0.1	100
	Heterogeneous effects	0	−0.1	0.1	0	99
	Web intervention slightly harmful	0	−0.1	−0.1	−0.1	99
	Web intervention harmful—small effect	0	−0.2	−0.2	−0.2	97
	Web intervention harmful—relatively small effect	0	−0.25	−0.25	−0.25	96
	Web intervention harmful—modest effect	0	−0.3	−0.3	−0.3	95
	Only arm B harmful	0	−0.35	0	0	86
	Web intervention harmful—moderate effect	0	−0.35	−0.35	−0.35	93
	Arm D very harmful	0	−0.3	−0.3	−0.6	97
	Observed effects until October 2023	0	Blinded	Blinded	Blinded	98
**PROMIS** ^a^ **anxiety (conditional on observed data; direction of effect reversed so that higher scores are better)**						
	No effect	0	0	0	0	92
	Arm B and arm C beneficial	0	0.2	0.2	0	91
	Web intervention slightly beneficial	0	0.1	0.1	0.1	96
	Heterogeneous effects	0	−0.1	0.1	0	89
	Web intervention slightly harmful	0	−0.1	−0.1	−0.1	84
	Web intervention harmful—small effect	0	−0.2	−0.2	−0.2	72
	Web intervention harmful—relatively small effect	0	−0.25	−0.25	−0.25	64
	Web intervention harmful—modest effect	0	−0.3	−0.3	−0.3	56
	Only arm B harmful	0	−0.35	0	0	73
	Web intervention harmful—moderate effect	0	−0.35	−0.35	−0.35	47
	Arm D very harmful	0	−0.3	−0.3	−0.6	17
	Observed effects until October 2023	0	Blinded	Blinded	Blinded	98

^a^PROMIS: Patient-Reported Outcomes Measurement Information System.

#### Missing Data

We will conduct complete case analyses for the primary analyses. If there are substantial missing data, we will repeat analyses using the multiple imputation methods by Raghunathan et al [72]. The multiple imputation analyses will be considered secondary sensitivity analyses to investigate how missing data might be affecting inferences.

#### Additional Secondary Analyses for Aim 1 (Amendment Added in July 2023)

As treatment effects might differ with changes in procedures related to the 21st Century Cures Act period (before vs after the implementation of immediate genetic test result release to patients at the University of Pennsylvania), we will estimate interaction regression models of the primary and secondary end point in which we include dichotomized period (0 or 1; no or yes; before July 2023 vs after July 2023), randomization arm, and the interaction between period and randomization arm (randomization arm indicators × period) as covariates in the model. In addition, we will examine interaction models in which we compare outcomes of people who receive results before their study protocol disclosure method appointment with those who do not receive results before their study protocol disclosure method appointment. We will exclude those who do not receive results at all in this secondary analysis examining the potential moderation effect of preappointment disclosure.

#### Moderator Analysis

We will evaluate moderators of outcomes, identifying those who benefit more and less from the intervention in clinical practice. For moderation (ie, effect modifier analyses), we will include in the generalized estimating equations–estimated regressions indicators (0 or 1 variables) denoting randomization arms, the potential moderator variable, and interaction terms between the moderators and randomization indicators (ie, an interaction term will be created by multiplying 2 terms). We will further examine 3-way interaction models in which we include time interactions. To maintain power to detect moderation, we will examine nontime moderators separately. We will also examine adding potential confounders to models. For all analyses, we will examine effects after assigning participants to intention-to-treat, per-protocol, and as-treated groups.

## Results

IRB approval was obtained in June 2019 and recruitment began in August 2020. We have completed the enrollment of 256 study participants and data collection was completed in September 2024. Data analysis is ongoing and we expect results to be published in Fall 2025.

## Discussion

### Expected Findings

We hypothesize that our digital delivery of pretest or posttest genetic counseling will yield equivalent or improved outcomes compared to the traditional 2-visit standard-of-care delivery model with a GC. This model has the potential to expand access to genetic services by leveraging digital technologies. For patients with metastatic cancers, access to genetic services is a necessary step to gain access to targeted therapeutic treatments, and our model may lead to improved access to targeted therapy reliant on germline genetic testing. We hypothesize that participants randomized to digital genetic counseling arms will experience noninferior changes in genetic knowledge and general anxiety compared to those randomized to the standard 2-visit genetic counseling model. We also predict that uptake of genetic testing, depression, cancer-specific distress, and health care provider time will be equivalent or improved in digital arms compared to the standard-of-care arm. Furthermore, we will explore demographic and clinical factors associated with uptake of the intervention and testing.

Several related studies looking at various alternative delivery models were ongoing at the time the eREACH study was designed and started recruiting [19-21,36,71,73]. Two studies among patients with prostate cancer (Technology-Enhanced Acceleration of Germline Evaluation for Therapy [TARGET] and ProGen) have been completed and found that digital pretest educational tools were noninferior to traditional genetic counseling [19,20]. TARGET used an educational web tool, and ProGen tested an educational video that was delivered to participants in person. Posttesting disclosure was performed by a GC in both studies [19,20]. The Making Genetic Testing Accessible (MAGENTA) study demonstrated that omitting pretest counseling for all participants and posttest counseling for participants without a pathogenic variant was noninferior to phone-based genetic counseling in terms of posttest distress [21]. MAGENTA included patients with breast cancer (3.3% of the total cohort) or a family history suggestive of a hereditary cancer syndrome but not patients with advanced or metastatic cancer. In addition, participants were highly educated (88.9% with some college education or higher) and mostly White individuals (95.3%) and likely represent an early adoption population; findings may be different in a diverse clinical population of patients with advanced cancer. While these studies support the premise that digital delivery alternatives may play a role in clinical genetics, there are no published randomized studies comparing the outcomes of using digital alternatives for returning genetic results to those of the traditional model of genetic counseling in metastatic cancer genetics (where testing is more complex and routinely now includes at least an option for multigene panels) and in diverse patient populations more reflective of real-world clinical practice. The eREACH study will address this gap in the literature by evaluating the efficacy of the proposed patient-centered digital delivery of pretest or posttest counseling for genetic testing among patients with metastatic breast or prostate cancer or advanced or metastatic ovarian or pancreatic cancer.

Another frequently endorsed model to increase uptake of testing is “mainstreaming,” wherein the traditional pretesting counseling session with a GC is replaced with educational materials and a conversation with a cancer care provider, such as an oncologist [15,74]. This provider orders the genetic test that they deem to be most appropriate, and results are disclosed by the medical provider with the option for a GC on patient request, when a positive result or a variant of uncertain significance is identified, or in the setting of a family history of cancer or a known familial mutation. A recent systematic review and meta-analysis identified 29 studies on mainstreaming, of which only 5 assessed patient-reported outcomes such as anxiety, depression, and decisional conflict [74]. Importantly, there are no published studies comparing mainstreaming to the traditional 2-visit genetic counseling model in which multigene panel genetic testing is offered. However, some of these studies include models that can be compared to arm C of the eREACH study (web intervention and GC), and we will be able to compare our patient-reported outcomes to those of studies that reported similar longitudinal measures.

The findings of this study will help determine whether the use of digital delivery of genetic counseling is an effective model for patients with metastatic cancers. If deemed noninferior, the eREACH study will provide an evidence base for a scalable digital model for genetic counseling for diverse and real-world patients with cancer in academic and community settings.

### Strengths and Limitations

We may encounter potential challenges in this study. Loss to attrition for the surveys may result in missing data. We will monitor completion rates during our quality control checks and assess and address barriers to survey completion during the study period. Inability to contact treating health care providers could result in missing data regarding the use of genetic test results for participants outside of the Penn Medicine system. Some health care providers may not be willing to serve as the ordering health care provider for genetic testing services. Although we have not experienced significant challenges with local physicians being willing to register with the Penn Telegenetics program, identifying and understanding barriers to oncologist uptake would be important for future implementation of this model. The financial burden of genetic testing may limit patient access to these services. We do not anticipate that this will be a common issue, but understanding these barriers to testing would also be important for future iterations of our delivery model. The inclusion of self-referred participants has the potential to introduce a selection bias wherein patients with higher digital literacy may be more likely to participate in this study. Given that this is a randomized trial, such participants should be evenly distributed between study arms, thus only potentially posing a threat to generalizability. To address generalizability, we will compare the digital literacy of the study population to that of the general population using available normative data from the Health Information National Trends Survey. Finally, our delivery model includes the involvement of a GC (even if there is no direct contact with the patient), whereas mainstream testing, with no involvement of GC, has become increasingly common. While we will not be able to conduct direct comparisons to these different delivery models in this randomized trial, we expect to be able to compare our results to those of other studies that may evaluate the outcomes of mainstream testing, assuming that they assess similar patient-reported outcomes and use similar measures.

